## Abstract

**Introduction:**

This study is designed to explore the baseline characteristics of patients under 55 years of age with a meniscal tear, and to describe the relationship between the baseline characteristics and patient-reported outcome measures (PROMs) over 12 months. Research has highlighted the need for a trial to investigate the effectiveness of arthroscopic meniscectomy in younger patients. Before this trial, we need to understand the patient population in greater detail.

**Methods and analysis:**

This is a multicentre prospective cohort study. Participants aged between 18 and 55 years with an MRI confirmed meniscal tear are eligible for inclusion. Baseline characteristics including age, body mass index, gender, PROMs duration of symptoms and MRI will be collected. The primary outcome measure is the Western Ontario Meniscal Evaluation Tool at 12 months. Secondary outcome measures will include PROMs such as EQ5D, Knee Injury and Osteoarthritis Outcome Score and patient global impression of change score at 3, 6 and 12 months.

**Ethics and dissemination:**

The study obtained approval from the National Research Ethics Committee West Midlands—Black Country research ethics committee (19/WM/0079) on 12 April 2019. The study is sponsored by the University of Warwick. The results will be disseminated via peer-reviewed publication.

**Trial registration number:**

UHCW R&D Reference: IA428119. University of Warwick Sponsor ID: SC.08/18–19

Strengths and limitations of this studyProspective study design: The study is prospectively designed which will reduce the risk of recall bias among participants.Multicentre design: By recruiting participants from multiple centres across the country, we are obtaining data from a range of physiotherapists and surgeons. This will ensure that the findings are representative of current UK National Health Service practice.Clearly defined outcome measures: We have preselected our patient-reported outcome measures (PROMs) which are widely used in previous meniscal research. This will enable comparisons with previous studies and also pooling of results in future reviews.Comprehensive clinical and radiological assessment of participants: We are including several important baseline features. This includes clinical history directly related to current British Association for Surgery of the Knee treatment guidelines. We are also the first study to explore the relationship between WORMS score and PROMs in patients with a meniscal tear.Absence of objective clinical outcome measures: A limitation of this study is that we are not reporting clinical outcome measures, for example, range of motion in the knee, muscle strength and return to sport.

## Introduction

Meniscal tears affect 60–70 per 100 000 of the population in the UK and account for 70 000 UK hospital admissions per year.^1 2^ Over recent years, there has been a substantial increase in meniscus-related literature, with a number studies questioning the effectiveness of surgical management.^3–5^

The meniscus is a highly specialised c-shaped structure located within the knee.^6^ It has an important role in distributing load across the knee joint, preventing damage to the articular cartilage.^7^ The meniscus is susceptible to tears or damage. Meniscal tears typically result from high energy twisting injuries, such injuries often occur during sporting activities.^8 9^ Meniscal pathology is also common in older people and is closely associated with osteoarthritis (OA) and age-related degeneration, which can lead to changes in the histology of the menisci and their mechanical properties.^10^

The current management of meniscal tears includes non-surgical options such as provision of advice and observation, physiotherapy or pharmacological options such as anti-inflammatory medication or intra-articular corticosteroid injections. Surgical options include meniscal repair (in limited cases) or arthroscopic partial meniscectomy (APM), a keyhole procedure performed with the intention of removing the torn or unstable meniscus which may be thought to cause pain or mechanical symptoms, for example, locking.^11^

Previous randomised controlled trials (RCTs) have found no evidence for a difference in outcome between APM and physiotherapy in patients with a meniscal tear and coexisting arthritis.^12 13^ This led to a change in National Institute for Health and Care Excellence guidelines advising against arthroscopic surgery to treat meniscal tears in the context of established arthritis.^14^ Abram *et al* performed a systematic review including studies comparing arthroscopic meniscectomy versus a comparator in patients with a meniscal tear.^4^ The authors included 10 studies for analysis and performed subgroup analysis for patients without OA. The authors reported a small improvement in knee pain for all patients with a meniscal tear in the meniscectomy group compared with the non-surgical group (standardised mean difference (SMD) 0.22 95% CI 0.04 to 0.4). Three studies reported pain scores in patients without OA, in which the authors found an increased improvement in pain scores in the meniscectomy group (SMD 0.35, 95% CI 0.04 to 0.66). There was a similar improvement in knee function in the meniscectomy group in patients without OA compared with all patients undergoing meniscectomy (SMD 0.18 vs SMD 0.3).

Despite the evidence challenging the clinical effectiveness of APM, there has been a 22% increase in the number of APMs performed over the last 20 years, from 151/100 000 in 1997 to 184/100 000 in 2017.^15–17^ Previous literature has provided evidence on the lack of effectiveness of APM in patients with a degenerative knee or arthritis as the symptoms may be caused by the degeneration and not the meniscal tear.^18 19^ UK national consensus statement from British Association for Surgery of the Knee (BASK) has highlighted the importance of patient factors which are important in the management of meniscal tears. The guidelines state patients with a particular pattern of meniscal tear visible on MRI (‘a meniscal target’) and the corresponding pattern of symptoms or signs should be recommended for non-urgent arthroscopy. Furthermore, patients should undergo a period of non-operative management before referral for APM.^20^ These guidelines also suggest that radiology investigations should be included in treatment decisions, with certain patterns of tears being ‘target’ lesions.^20^ A future cohort study will need to assess the importance of the MRI tear pattern as an outcome predictor.

A well-designed cohort study needs to be performed with patients being recruited at the point of diagnosis or presentation to an orthopaedic specialist. This will allow researchers to include patients being managed non-operatively. By including MRI analysis in a potential predictive model, this will produce a comprehensive model to identify which features can predict variability in patient-reported outcome measures (PROMs).

### Study aim

To describe the baseline characteristics and imaging findings of young patients with a meniscal tear and to explore the relationship, if any, between these baseline features and 12-month outcomes.

We will address the following research objectives:

Describe the baseline characteristics, pattern of symptoms and imaging findings of younger people (aged <55 years) with a meniscal tear (study population).Explore the relationship between these features and 12-month PROMS.

## Methods and analysis

A multicentre prospective cohort study will be performed. The study obtained approval from the National Research Ethics Committee (NRES) West Midlands—Black Country research ethics committee (19/WM/0079) on 12 April 2019. All patients presenting to a secondary care centre (elective knee clinic or acute knee clinic) with a MRI confirmed meniscal tear, under the care of orthopaedic consultants at any of the participating sites, will be invited to take part in the study. The following eligibility will be implemented for patient selection.

Inclusion criteria:

Age between 18 and 55 years.Presence of an MRI confirmed meniscal tear.Provision of informed written consent.

Exclusion criteria:

Anterior cruciate ligament or other major knee ligament injury. This does not include a previous unrelated healed medial collateral ligament tear or a meniscal root tear (which is considered a type of meniscal tear in this study).Associated intra-articular fracture of the tibial plateau or femur. Previous fractures not thought to be related to the tear are not an exclusion criteria for the study.Previous knee surgery, for example, unicondylar knee replacement; total knee replacement; knee arthroscopy; meniscal repair or meniscectomy.Previous entry into the present study (ie, the other knee).Participant is unable to undertake study procedures.

### Participant identification and screening

Potential participants will be identified by a member of the attending clinical team or a member of the clinical research team by screening clinic lists in secondary or intermediate care clinics. This will involve a member of the clinical team reviewing letters for the upcoming knee or orthopaedic clinics to identify potential participants.

Eligibility will be confirmed based on assessment and standard care MRI. In normal clinical practice, MRI is a requirement for diagnosis of a meniscal tear, therefore, all participants entering the study will already have had one at the time of entry into the study.

All individuals who meet the study entry criteria will be checked for eligibility and recorded on the monthly screening log. Eligible potential participants who are willing to be approached by a suitably trained member of the research team will be provided with verbal and written information about the study, and will have the opportunity to discuss and ask questions.

### Baseline data collection

Once participants have provided informed consent, baseline data will be collected by the research team. Baseline characteristics such as age, gender, body mass index and date of potential injury and duration of symptoms will be collected. Baseline PROMs will be collected at recruitment in order to assess changes in PROMs at 12 months. Clinical features which are consistent with a treatable meniscal lesion, outlined by the BASK consensus meeting, will also be collected from the attending clinician (for a locked knee) and the participant (for locking and catching).^20^ These include the presence of:

Locked knee: sudden onset, complete mechanical block to flexion or extension of the knee, detected on clinical examination and which does not resolve despite adequate analgesia.Locking: an intermittent block to normal range of movement of the knee (commonly a block to extension) with an associated unlocking movement. Knee returns to near normal after unlocking.Catching: the sensation of something intermittently out of place in the knee and interfering with joint movement.

These will be assessed on initial baseline questionnaires which will be provided by the host site. If the clinician documents specific examination findings (in particular alignment), this will be collected by the study team.

MRI scans will be analysed to assess:

Anatomical location and tear pattern. Tear patterns include the following which have been recognised by BASK as potentially treatable ‘meniscal targets’.^20^
Bucket handle tear: a longitudinal tear involving more than 25% of the meniscus length (can be displaced or undisplaced).Displaced meniscal tear: fragments are displaced from their usual anatomical position.Meniscal root tear.Radial tear: a vertical tear which may or may not extend into the meniscocapsular junction.Horizontal tear.Complex tear: a meniscal lesion with more than one place of tear in continuity.Whole-Organ MRI Score (WORMS): This is a semiquantitative, multifeature scoring method for whole-organ evaluation of the knee using conventional MRI. It is based on 14 features include cartilage and meniscal integrity.^21^

### Primary outcome

Western Ontario Meniscal Evaluation Tool (WOMET) at 12 months. This is a meniscal tear disease-specific quality of life measure developed in collaboration with patients in 2007. It consists of 16 questions (items) focusing on three domains: (1) physical symptoms, (2) sport/recreation/work/lifestyle and (3) emotions. Items are assessed on a Visual Analogue Scale (VAS), summed and reported as a percentage of the maximum score of 1600.^23^ A recent systematic review of PROMs used for meniscal research demonstrated that WOMET had the strongest evidence for content validity.^24^ It is also one of the only PROMs developed with the involvement of patients with meniscal tears as their primary diagnosis.

### Secondary outcomes

WOMET: collected at baseline, 3 and 6 months: as outlined above.Knee injury and Osteoarthritis outcome score 4 (KOOS)^25^: The KOOS questionnaire was developed in 1998 as a knee injury-specific outcome measure of patients at risk of developing arthritis.^26^ Domains are pain, symptoms, functional status, sports activity and quality of life. It is used extensively in knee injury research, and has been the primary outcome in the majority of clinical trials studying the treatment of meniscal tears. In previous meniscal tear research a shorter form of KOOS (KOOS_4_) has been widely used.^25^ This focuses on four out of five of the domains pain, symptoms, sport and recreational function and quality of life. Standardised answer options are provided using a Likert scale and each question is assigned a score of 0–4. A score of 100 indicates no symptoms whereas a score of 0 indicates extreme symptoms. This outcome tool can be used as a postal or electronic survey and both versions are comparable with regard to psychometrics.^27^ KOOS4 will be collected at baseline and 12 months only.EuroQol (EQ-5D-5L (EuroQol-5 domains- 5levels): This is a validated measure of health-related quality of life, consisting of a five-dimension health status classification system and a separate VAS. EQ-5D is applicable to a wide range of health conditions and treatments and provides a simple descriptive profile and a single index value for health status, range from −0.594 to 1, and anchored at 0 (death).^28 29^ EQ-5D is primarily designed for self-completion by respondents and is ideally suited for use in postal surveys, in clinics and face-to-face interviews.^30 31^ It is cognitively simple, taking only a few minutes to complete.^29 32^ This will be collected at baseline, 3 months, 6 months and 12 months.Patient global assessment of change (PGIC): A simple 7-point scale assessing participant perception of improvement.^33^ A standardised question will be used to explore the change in activity limitations, symptoms and quality of life in the painful knee. Responses will range from ‘no change or condition has worsened’ to ‘a great deal better. This will provide valuable information for a future large scale trial by providing information on the minimally clinical important difference in WOMET score for this patient population. This will be collected at 3 months, 6 months and 12 months.Surgery: We will also collect data on whether participants undergo surgery for their meniscal tear. At each time point (3, 6 and 12 months) patients will be asked if they underwent surgery. We will continue to follow up patients after surgery to determine their outcome in a pragmatic fashion, as would happen in the conservative arm of a large trial.

These PROMs will be collected at baseline, 3, 6 and 12 months from the date of recruitment. Data will be collected using questionnaires designed with patient and public involvement. This data will be collected by a number of methods (either postal, telephone, electronically or face to face) dependent on participant preference. If a participant requests face-to-face consultation or has difficulty reading or writing, a clinic visit will be arranged.

### Sample size calculation

Previous experience^34^ for studies of this type, where statistical models have been built to explain variation in PROMs, suggests that they rarely explain more than 10%–20% of the variation in outcomes (R^2^) at 12 months. Using a large (and therefore rather conservative) estimate for the numerator number of df of 25 (ie, the model complexity) for a putative F test of the model significance and an R^2^=0.1, suggests a sample size of 160 for 90% power at the 5% significance level (https://cran.r-project.org/web/packages/pwr/; pwr.f2.test).^35^ Experiences of previous such studies in similar settings have reported follow-up rates of 80%. Assuming lost to follow-up of 20%, 200 participants will be required for this study.

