## Discussion

This prospective cohort study aims to describe the baseline characteristics of young people (age <55) with a meniscal tear and to explore the relationship between these features at outcome. This study has a role in informing treatment decisions by identifying in certain patient features can predict treatment outcome. There is a view among researchers and clinicians that surgery may be beneficial among a particular subset of patients and further research is needed to identify this subset.^4^ This work will assist in the future planning of an RCT by further exploring the study population. The study aims to identify the patients that improve with both operative and non-operative management and whether there are certain factors which influence the response to either treatment. It may be that in a population of patients who do not improve with non-operative care and do not have features of arthritis, that a study is required to assess the effectiveness of surgery, but before this can be performed, we need a much better understanding of the characteristics of this population and how they might be defined. This cohort study will also inform a future trial by providing an insight into follow-up rates in this younger population, efficient means of collecting outcome data, and also providing an understanding of the MCID of the WOMET score.

This study aims to build on a previous cohort study which was performed in order to identify features which may predict variability in PROMs for patients following arthroscopy. The authors included 18 preoperative factors and found the strongest predictive factors were no previous meniscal surgery and more severe preoperative knee symptoms. However, factors such as tear pattern or structural OA were not assessed as preoperative imaging was not available to the authors, and so our study will answer a related, but different question. The models overall predictive performance was very low (optimum adjusted R^2^=0.080) suggesting the included factors had little relevance to outcome.^5^ The authors only included patients undergoing operative intervention, work is needed to identify outcomes in all patients that are managed with a meniscal tear, in order to identify which patients performed well with non-operative management and which perform poorly.

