An upper age limit of 55 was selected, as the mean age in a recent meta-analysis of trials in meniscal tears. As the one of the purposes of the study is to explore the relationship between baseline data and outcome, we will explore the effects on age. Age was not an important factor in the recently published analysis of the Knee Arthoscopy Cohort Southern Denmark (KACS) cohort and while it may be relevant, it may also be a poor proxy for other relevant factors, such as underlying OA or meniscal degeneration. This will be explored in this study and, if age is important, the study will allow us to set evidence-based thresholds for future research.

Strengths of the METRO cohort include its prospective nature, minimising the risk of participant recall bias. We are also reporting outcomes in all patients with a meniscal tear including both the operative and the non-operative group, this ensures the study results are more representative of all patients with a meniscal tear. The multicentre national nature of this study ensures that the data included are generalisable to current UK practice, especially after publication of the national treatment guidelines.^20^ Further strengths include the use of MRI based assessment of tear pattern, arthritis and bone shape change which could be an important predictive factor for outcome.

Limitation of this study design in comparison to previous research is our sample size is smaller than a previous study which did not identify any predictive factors,^5^ however, this study did not include MRI data and we have included a thorough sample size calculation with a conservative estimate of the number of df. In addition, this observational study will provide an insight into associations between patient factors and PROMs, however, as the study is observational the findings will be utilised for generation of new hypotheses and causal inference will be limited, and will require further study in RCTs. A multicentre RCT is currently recruitment comparing surgery versus physiotherapy, however, the eligibility criteria do not take into account presence of OA on MRI.^39^ This cohort study will explore whether that is an important factor in patient outcome.

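### With the protocol's own inputs (R²=0.1, 25 df, 5% level), 160 completers give about 58% power, not 90%, and about 45% at the R²=0.08 of the earlier meniscal cohort

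*Protocol article*

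**What the plan says.** The Sample size calculation section starts from experience that models explaining patient-reported outcomes "rarely explain more than 10%–20% of the variation in outcomes" at 12 months. It takes a "numerator number of df of 25 (ie, the model complexity) for a putative F test of the model significance", which it describes as conservative. It then says that "R^2^=0.1, suggests a sample size of 160 for 90% power at the 5% significance level", naming the `pwr.f2.test` routine. With 20% loss to follow-up, 160 becomes 200 recruited.

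The Discussion describes an earlier cohort of patients undergoing arthroscopy, modelled on 18 preoperative factors. Its "overall predictive performance was very low (optimum adjusted R^2^=0.080"), and "the strongest predictive factors were no previous meniscal surgery and more severe preoperative knee symptoms". Among the exclusion criteria in Methods and analysis is previous knee surgery, with examples that include "knee arthroscopy; meniscal repair or meniscectomy".

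Further on, the limitations paragraph of the Discussion acknowledges that the present sample is smaller than that of "a previous study which did not identify any predictive factors". This is the same cited study (reference 5). The paragraph answers with the added MRI data and the conservative degrees of freedom.

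**The concern.** There are two questions: whether 160 follows from the stated inputs, and whether R²=0.1 is a safe input.

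On the second, a range that models seldom exceed describes a ceiling, so its lower end is not automatically cautious. The one numerical R² that the article gives for an earlier meniscal cohort is the best value that cohort reached, and it lies below 0.1. Part of what produced it cannot vary here, because people with previous meniscal surgery are excluded. The sample size section does not mention this figure.

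What is at stake is how a negative result would be read. A reader who believes the study had 90% power could take a non-significant overall F test as evidence that baseline and MRI features do not matter. If the true power is near or below one half, that inference fails. The study is meant to inform a future randomised trial, so the stated power should be right.

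**Working it through.** **Inputs.** From the Sample size calculation section: R²=0.10, u=25 numerator df, α=0.05, target power 0.90, N=160 completers, 20% loss. From the Discussion: adjusted R²=0.080 in the earlier cohort. R²=0.05 is an assumption, used only to show a lower case. Adjusted R² is taken as an estimate of the population R² that enters the power formula.

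**Method.** This is the calculation behind the routine the article names:
- f² = R²/(1−R²)
- v = N − u − 1
- λ = f² × (u + v + 1) = f² × N
- power = P[F′(u, v, λ) > F₀.₉₅(u, v)], where F′ is the noncentral F.

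**Attempt to reproduce the 160.**
- f² = 0.10/0.90 = 0.111.
- Solving for 90% power gives v = 248.7, so N = 248.7 + 26 = 274.7, rounded up to **275** completers. Recruited: 275/0.8 = 343.75, so **344**.
- The dropout step in the article is correct: 160/0.8 = 200.
- Slips that might explain 160 do not. Entering 0.1 directly as f² gives 303. Using λ = f² × v gives 299. Reporting v instead of N gives 249. Using 80% power gives 226.
- Figures near 160 appear only if a stated input changes. Entering f²=0.20 directly (R² about 0.167) gives 162, and 6 df at R²=0.1 gives 164.

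**Power at N=160** (v = 160 − 26 = 134, critical F(25,134) = 1.588):

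| R² | f² | λ = 160 × f² | Power |
|---|---|---|---|
| 0.10 (planned) | 0.1111 | 17.8 | 58.0% |
| 0.08 (earlier cohort) | 0.0870 | 13.9 | 44.9% |
| 0.05 (assumption) | 0.0526 | 8.4 | 25.8% |

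Solving the other way, 160 completers give 80% power at R² of about 0.140 and 90% at about 0.168. Even if all 200 recruits were followed up, power at R²=0.10 would be 72.7%.

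**How the shortfall divides.** From the stated 90% to 58.0% is 32.0 points, and this arises at the plan's own R². From 58.0% to 44.9% is a further 13.1 points, which comes from moving R² to 0.08. If N were corrected to 275, power at R²=0.08 would be 78.5%. For 90% at R²=0.08, 346 completers would be needed, or 346/0.8 = 432.5, so 433 recruited.

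**The two descriptions of the earlier cohort.** One Discussion paragraph names its strongest predictive factors. The limitations paragraph says it found none. The citation is the same, so both cannot stand as written.

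**The case against.** A reader might infer that the 90% fails because R²=0.1 is too optimistic, and that the plan must move to 0.08 or lower. The documents do not support that reading.

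- Most of the gap arises at R²=0.1 itself, so the choice of R² is not the main cause.
- 0.10 is the low end of the range the section cites, and that range comes from a different source that is not available here.
- The Discussion says the earlier cohort contained only operated patients and had no imaging, and that the present study asks a related but different question. Tear pattern, WORMS and bone area are added here and may explain more.
- The two strongest predictors are not ranked. Only previous surgery is excluded; symptom severity remains available through the baseline PROMs. The article does not say how much of the 0.080 came from previous surgery, so any value below 0.08 is an assumption.

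All of this stands, and it makes the choice between 0.10 and 0.08 a judgement. It does not rescue the 90%, which fails at 0.10.

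It can also be said that the F test is called putative, that the Statistical analysis section sets no decision rule on it, and that the findings are meant to generate hypotheses. That limits the harm, and the article nowhere says that a null F test would be read as absence of association. But the F test is the only stated basis for the sample size, so its power should be reported correctly.

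**Conclusion.** The stated power is wrong for the stated inputs: about 58% rather than 90% at 160 completers, with 275 needed for 90%. This rests only on the article's own R², degrees of freedom and significance level, and on the routine it names.

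The sensitivity to R² is a secondary point. At the earlier cohort's 0.08, power is about 45%, so a non-significant overall test would then be slightly more likely than a significant one. At an assumed 0.05 it is about 26%. A planning value of 0.10 is not disproved, but the article does not show it to be conservative. The conservative choice of 25 df does not protect the calculation either, since its effect on N is not reflected in the 160.

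The contradiction about the earlier study is a real but small wording error. It has no bearing on whether 0.10 is right.

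**What to change.** In the Sample size calculation section, replace the 90% claim with the actual power of the overall F test at 160 completers and 25 df: about 58% at R²=0.10. Beside it, give 45% at R²=0.08, citing the earlier cohort in the Discussion, and 26% at R²=0.05, labelled as an assumption. Add a sentence saying that, at this power, a non-significant overall F test is not evidence that baseline and MRI features are unrelated to outcome. If the authors used inputs other than those printed, they should state them.

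In the limitations paragraph of the Discussion, reword the statement about the earlier study so that it agrees with the earlier account: it named predictive factors, but its model explained little of the variation.

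This is a change of wording only and needs no extra patients or data. The cost is a less favourable stated power. Keeping a 90% target would be a different decision, with 275 completers (344 recruited) at R²=0.10 or 346 (433 recruited) at R²=0.08.

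### The 25 model df are called conservative without a count, and at R² = 0.10 the planned 160 evaluable patients give about 58% power, not 90%

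*Protocol article*

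**What the plan says.** All of this is in the protocol article.

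- **Sample size calculation.** The model complexity is introduced with "Using a large (and therefore rather conservative) estimate for the numerator number of df of 25", "for a putative F test of the model significance and an R^2^=0.1". The result is given as "suggests a sample size of 160 for 90% power at the 5% significance level", followed by "Assuming lost to follow-up of 20%, 200 participants will be required for this study". The choice of R² rests on experience that models of this kind show "they rarely explain more than 10%–20% of the variation in outcomes".
- **Discussion, limitations paragraph.** The article concedes that the cohort is smaller than an earlier one and answers, in part, that "we have included a thorough sample size calculation with a conservative estimate of the number of df".
- **Baseline data collection.** The section lists demographics, symptom history, baseline PROMs, three mechanical symptoms, tear location and pattern, WORMS, bone area and cartilage volume. Of WORMS it says "It is based on 14 features include cartilage and meniscal integrity".
- **Statistical analysis.** A linear model is the first choice. Baseline data are named only as an example of what may enter it.
- **Discussion, opening paragraph.** It adds the wish to learn "whether there are certain factors which influence the response to either treatment".

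**The concern.** At a fixed R², a larger numerator df raises the required sample size. Calling 25 large is therefore a claim that the sample size errs on the safe side. The article makes this claim twice, and the second time it serves as a reply to an acknowledged limitation. It would be sound if 25 clearly exceeded the df of the intended model and if 160 followed from 25 df and R² = 0.10. The article shows no count to support the first condition, and the second condition fails.

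A reader who accepts the wording will think the overall model test has at least 90% power with something in reserve. If the true figure is nearer 58%, a non-significant model says little about whether baseline and MRI features matter. That question is the study's second objective, and the answer is meant to inform a later randomised trial.

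**Working it through.** **1. Inputs (Sample size calculation).** u = 25 numerator df; R² = 0.10; significance level 5%; power 90%; N = 160 evaluable; 20% loss.

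**2. Formula.** This is the overall F test as in the function the article cites:

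- f² = R²/(1 − R²) = 0.10/0.90 = 0.1111
- v = N − u − 1
- λ = f² × (u + v + 1) = f² × N
- power = P[F′(u, v, λ) > F₀.₉₅(u, v)], where F′ is non-central F

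**3. The plan's own figure.** At N = 160 and u = 25, v = 134, λ = 0.1111 × 160 = 17.78 and the critical F is 1.588. Power is 0.580. The 160 is not reproduced. Solving for 90% power gives v = 249, so N = 249 + 25 + 1 = 275. Recruitment at 20% loss is 275/0.8 = 343.75, or 344. The step from 160 to 200 (160/0.8) is correct.

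**4. What would give about 160.** With u = 25, f² = 0.20 (R² = 0.20/1.20 = 0.167) gives N = 162. With R² = 0.10, u = 5 gives N = 154 and u = 6 gives N = 164. The documents do not show whether either explains the stated figure.

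**5. Df count from the listed variables.** The article gives none. This count takes linear main effects and depends on coding.

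| Variables | Compact | Detailed |
|---|---|---|
| Age, gender, BMI, symptom duration | 4 | 4 |
| Baseline PROMs: the matching one only, up to WOMET, KOOS4, EQ-5D index and EQ VAS | 1 to 4 | 4 |
| Locked knee, locking, catching | 3 | 3 |
| Tear location | 1 | 1 |
| Six tear patterns (exclusive categories, or yes/no indicators) | 5 | 6 |
| WORMS (total, or 14 features) | 1 | 14 |
| Bone area, cartilage volume | 2 | 2 |
| **Total** | **17 to 20** | **34** |

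Against 25, compact coding leaves 25 − 20 = 5 to 25 − 17 = 8 df spare. Detailed coding is 34 − 25 = 9 df over.

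**6. Power across that range** (R² = 0.10, 5% level):

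| df | Power at 160 evaluable | Evaluable N for 90% | Recruited at 20% loss |
|---|---|---|---|
| 5 | 91% | 154 | 193 |
| 17 | 69% | 236 | 295 |
| 20 | 65% | 252 | 315 |
| 25 | 58% | 275 | 344 |
| 34 | 48% | 312 | 390 |

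**7. Separating the two effects.** The gap between the stated 90% and 58% at 25 df is 32 points, and it arises because 160 does not follow from its inputs. The df count alone moves power from 58% to 65% at 20 df (+7 points) or to 48% at 34 df (−10 points). If N were the 275 that 25 df requires, 34 df would still give 84%.

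**The case against.** The tempting stronger reading is that the listed variables already use up the 25 df, so there is no margin at all. The documents do not support it, for four reasons.

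- 25 lies inside the range of 17 to 34, and compact coding leaves 5 to 8 df spare. The one comparator in the article, the earlier cohort, used 18 factors.
- The 34 df case needs all 14 WORMS features as separate predictors. The article calls WORMS a scoring method and speaks of relating the WORMS score to PROMs, so one score is the more natural reading.
- Collecting a variable does not commit it to the model. Which variables enter, and how they are coded, is commonly left to an analysis plan, which is not shown here.
- A reader might also infer from "whether there are certain factors which influence the response to either treatment" that surgery and all its interactions belong in the powered model. The study aim and objectives do not say so, the Statistical analysis section describes a linear weighted sum, and the Discussion treats the findings as hypothesis-generating.

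These points stand, and so does the direction of the authors' reasoning: more df at fixed R² does raise N. It can also be said that a higher R² rescues the design, since at R² = 0.20 and 25 df, 160 evaluable give 96% power. That is correct, but 0.20 is the top of the range the article considers and 0.10 is the value it chose. The earlier cohort's best adjusted R², as reported in the Discussion, was 0.080, though without MRI data.

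None of this rescues the word conservative. At R² = 0.10, power at 160 is below 70% even for the most compact count.

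**Conclusion.** The point holds in a limited form. The description of 25 df as large and conservative is unsupported, because no count is given. The margin is modest under compact coding and negative under detailed coding. It cannot be said that no margin exists.

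The firmer conclusion is that the calculation as a whole is not conservative. On its own inputs, 160 evaluable give about 58% power, and 90% needs 275. At R² = 0.10, 160 reaches 90% for only about 5 df.

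The power figures rest on the overall F test with R² = 0.10 as total explained variance, the 5% level and exactly 160 analysed. They do not depend on how the variables are coded, except through u. The df counts are an assumption about coding and are shown as a range for that reason.

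**What to change.** 1. In Sample size calculation, state the power that 160 evaluable patients deliver at 25 df and R² = 0.10, about 58%. Alternatively, reconcile R², df and N so that the three agree, and say which was changed.
2. Remove the description of the df as large and rather conservative there, and the word conservative in the limitations paragraph of the Discussion.
3. State that the primary WOMET model will use at most the 25 df assumed in planning. The coding that achieves this can be left to the analysis plan.
4. Label any treatment-by-feature analysis as exploratory and outside the powered model.

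The cost is a few sentences of protocol wording. The downside is a less favourable stated power. Keeping 90% at 25 df and R² = 0.10 would instead mean recruiting 344 rather than 200. Changing the df wording alone would not repair the calculation, because 160 does not follow from R² = 0.10 at 17, 20, 25 or 34 df.
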